Facilities and Senior High Rises that are involved in providing services to the residents. They could be activity directors, social workers, outreach coordinators, care coordinators, etc. These individuals are not specifically trained to deliver exercise interventions as part of their job. We will work with our community stakeholders and the building managers to identify staff activity personnel at each of the sites who would be involved in this research study. All exercise leaders and identified staff activity personnel will be trained in the delivery of the exercise program prior to leading any exercises classes. The staff activity personnel will participate in a one hour training sessions in which the rationale and the general format of the program will be explained. During these training sessions the activity staff personnel will participate in a sample exercise class. In addition to the 2 training sessions, the activity staff personnel will be able to observe the 12 week exercise session delivered by the exercise leader at their facility. They will be given the opportunity to observe all 24 sessions if they would like. In addition to training the exercise leaders and activity staff personnel, we will provide printed materials explaining the exercise program that we developed in our pilot work (see appendix). After training, the exercise leader will determine if the staff activity personnel is ready to lead the exercise class. The exercise leader will consider the following when determining if the individual is ready to lead the class: 1) attendance at training sessions, 2) attendance at exercise sessions, 3) interactions with research participants, and 4) understanding of the exercise program including all safety considerations. A study investigator ([name] or [name] or one of the exercise leaders) will meet with the staff activity personnel or email them periodically (i.e. during weeks 1, 3, 6, and 10 of the 12 week exercise program) to observe the intervention, monitor treatment fidelity, and to answer any questions. If the study team believes the staff activity person is not ready to lead a class safely and per protocol at a particular site, their class will also be led by an exercise leader.

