### **8.2 Intervention Discontinuation**

At any time, the study team may recommend discontinuation of any component of the intervention or intervention group of the study for any of the following reasons:

1. Compelling evidence from this or any other study of an adverse effect of the study intervention(s) that is sufficient to override the potential benefit of the interventions to the target population
2. Compelling evidence from this or any other study of a significant beneficial effect of the study intervention(s), such that it is continued denial to other study group(s) would be unethical
3. A very low probability of addressing the study goals within a feasible timeframe.

The research team may decide at any time to remove a participant from the research study if the team feels the participant is unsafe to continue. Participation in the research study will be discontinued if a participant's walking ability worsens; for example, if a subject who has osteoarthritis of the knees exhibits a significant increase in pain that negatively affects their walking ability. Participants can be removed from the study if they have unstable vital signs as a response to exercise. A participant can also be removed from the study if any new medical condition, injury or illness is discovered during the course of treatment that would make the participant unsafe to continue.

The research team may decide at any time to discontinue training of a staff activity person if the teams feels the staff activity person is unsafe to continue. If training of a staff activity person is discontinued, an exercise leader will take over as instructor for the exercise class to keep our obligation of the exercise class to the community. If such a change becomes necessary after the class has begun, we will exclude that particular class from all analyses. If such a change becomes apparent before the class begins, and the entire class is taught by an exercise leader, we will include the class in Aim 1 analysis.

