## 9 STATISTICAL CONSIDERATIONS

### 9.1 General Design Issues

A randomized trial is needed to control for confounding factors that affect the outcome. There are no ethical issues regarding a randomized trial since both groups will be receiving an active exercise intervention delivered by trained personnel. We carefully considered the advantages and disadvantages of randomizing at the level of the facility and the resident. Given the amount of interaction that occurs between subjects within a facility, it is imperative that we conduct a cluster randomized trial, and randomize by facility to exercise programs. If we randomize at the resident, participants would discuss details of their intervention and cause cross-contamination between the intervention arms. Unlike a traditional trial in which participants are randomized as they are being recruited, a cluster randomized trial also affords the additional benefit of examining the facility characteristics such as type (independent living/senior high rise) and size, and ensuring a balance in those characteristics is achieved by design rather than chance. Once the facilities are randomized to exercise program, we will then randomize within facility for delivery mode (i.e. subjects will be randomized to either an exercise leader or staff activity person led exercise program). Randomization for delivery mode will occur after baseline testing. We will use a commercially available high quality pseudo-random deviate generator such as that available in SAS® (SAS Institute, Inc., Cary, North Carolina) known to be free of serial correlations(56) to randomize facilities to the two arms in a 1:1 ratio, stratified by facility type. In addition, the proposed design reaps the advantages of a paired comparison for the exploratory hypothesis (Aim 2) as both exercise leaders and staff activity personnel will be delivering On the Move in the same set of facilities, where feasible to train a staff person ready to lead the class safely and per protocol.

The main outcomes are self-reported function and disability (Late Life Function and Disability Index/LLFDI) and walking ability (6-minute walk test/6MWT and gait speed). We will also examine satisfaction, attendance rates and adverse event (falls, soft tissue injuries, muscle soreness, etc) rates.

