|----------------------------|----------------------------------|---------------------------------|-----------------------------------------|------------------------------------------------------------|---------------------------------|-----------------------------------------------------------------------------|---------------------------------------------------------------------------------------|
|                            | Baseline Standard Deviation (SD) | SD in Baseline-Follow up Change | Meaningful Difference Targeted (Source) | Completers
Needed Per Arm assuming No Clustering | Number Needed to Enroll Per Arm | Facility Staff as Good as Exercise Leader in Delivering OTM?
N=140 vs 60 | OTM More Effective than Standard Even when Delivered by Facility Staff?
N=60 vs 60 |
| LLFDI Overall Function     | 6.15                             | 4.86                            | 3.08 ( $d=0.5$ )                        | 66                                                         | 70                              | 98%                                                                         | 93%                                                                                   |
| LLFDI Disability Frequency | 6.35                             | 4.76                            | 3.18 ( $d=0.5$ )                        | 60                                                         | 60                              | 99%                                                                         | 95%                                                                                   |
| Gait Speed (m/s)           | 0.13                             | 0.20                            | 0.10                       | 105                                                        | 110                             | 90%                                                                         | 78%                                                                                   |
| 6MWD (m)                   | 62.0                             | 42.8                            | 50                         | 21                                                         | 30                              | >99%                                                                        | >99%                                                                                  |

1031  
 1032  
 1033

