#### 9.3.3 Aims 2, 3(b) and 4 exploratory Analyses

##### Aim 2:

We propose an analytic strategy with an exploratory philosophy for Aim 2 sustainability aim, because of the uncertainty surrounding our ability to recruit and train a staff activity person to lead a class safely and per protocol.

We will fit a series of linear mixed models using the SAS® MIXED procedure with baseline to follow-up change in each of the continuous outcomes (LLFDI function/disability, walking ability, other measures of mobility performance) as the dependent variable; intervention arm (standard/*On the Move*), delivery mode (by exercise leader/staff activity personnel) and their interaction as fixed effects of interest; baseline value of outcome and any other measures found to be different between arms or deemed important as additional fixed effects covariates; and a facility random effect to account for greater similarity of participants from the same facility compared to different facilities and resulting non-independence of observations within facility (ie. clustering). We will construct appropriate means contrasts to estimate difference in gains in the two interventions when delivered by staff exercise personnel (Aim 2 effectiveness hypothesis); and difference in gains attributable to *On the Move* intervention when delivered by exercise leaders and staff activity personnel (Aim 2 sustainability hypothesis). Statistical significance of the estimates will serve as formal tests hypotheses. We note that participants randomized to staff activity personnel had to wait 12 weeks since their baseline assessment and randomization to start the intervention, during which they may have changed; and that they underwent a second baseline assessment immediately prior to starting the exercise intervention. Therefore, we will repeat the above analysis using their second baseline assessment instead of the first one to assess the sensitivity of results.

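### The staff-led On the Move versus Standard contrast depends on a readiness judgement made after the program is assigned, yet it is formally tested as an effectiveness hypothesis with no as-randomised check

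*Supplement*

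**What the plan says.** All references are to protocol Version 2.0.

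- **Order of assignment (9.1):** "Once the facilities are randomized to exercise program, we will then randomize within facility for delivery mode".
- **Training (Section 3, Choice of comparators):** beyond the training sessions, "the activity staff personnel will be able to observe the 12 week exercise session delivered by the exercise leader at their facility". What staff observe is the program already assigned to their building.
- **Readiness (same section):** "After training, the exercise leader will determine if the staff activity personnel is ready to lead the exercise class". Four things are weighed: attendance at training, attendance at exercise sessions, interactions with participants, and "understanding of the exercise program including all safety considerations". If the study team finds the person not ready, "their class will also be led by an exercise leader".
- **Analysis of switched classes (8.2):** if the need for a change shows before the class begins and "the entire class is taught by an exercise leader, we will include the class in Aim 1 analysis". If the change comes after the class has begun, the class is left out of every analysis.
- **Aim 2 analysis (9.3.3):** mixed-model contrasts will "estimate difference in gains in the two interventions when delivered by staff exercise personnel (Aim 2 effectiveness hypothesis", and their statistical significance is to serve as the formal test. The one sensitivity analysis specified there for Aim 2 substitutes the second baseline for the first.
- **Power (9.2, Table 4):** under the column question "OTM More Effective than Standard Even when Delivered by Facility Staff", with 60 versus 60 participants, power is given as 93%, 95%, 78% and >99% for the four outcomes.
- **General principle (9.3.1):** all analyses follow intention-to-treat. Section 9.3.4 lists an as-treated analysis only as an additional one.

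**The concern.** Randomising facilities makes the two programs' facilities comparable on average. That holds for all facilities randomised. It does not automatically hold for the subset whose staff member was later judged ready and kept leading. The judgement follows program assignment, is made by someone who delivers the assigned program and so must know it, and partly concerns that program's content and safety. On the Move is progressive and mostly standing. Standard is mostly seated and modelled on what facilities already run. A different share of staff could therefore pass in each arm, leaving differently selected facilities on the two sides of the staff-led contrast.

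At stake is what may be concluded for Aim 2. A significant staff-led difference would be reported as effectiveness under staff delivery, with nothing telling the reader that the comparison was restricted after randomisation. Adjusting for participants' baseline measures does not directly address selection of staff or facilities.

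**Working it through.** **1. Does readiness decide who is analysed?** The steps run: program assigned to facility; staff trained and able to watch that program; readiness judged; class led by staff or by a leader. Under 8.2 a leader-taught class goes to Aim 1 or to no analysis. Section 9.3.3 does not say whether delivery mode is coded as assigned or as delivered. Given 8.2, as delivered is the natural reading, so the staff-led arms hold only facilities whose staff passed and stayed. Section 9.3.1 points the other way, and the two are not reconciled.

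**2. The plan's power figures.** With n = 60 per arm and two-sided alpha 0.05, power is approximately Φ(δ / (SD·√(2/60)) − 1.96):

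| Outcome | δ | SD of change | Power | Stated |
|---|---|---|---|---|
| LLFDI function | 3.08 | 4.86 | 93.5% | 93% |
| LLFDI disability frequency | 3.18 | 4.76 | 95.5% | 95% |
| Gait speed (m/s) | 0.10 | 0.20 | 78.2% | 78% |
| 6MWD (m) | 50 | 42.8 | >99.9% | >99% |

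The stated figures reproduce. They treat the contrast as a clean two-group comparison and carry no allowance for selection.

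**3. How large could the bias be?** From the plan: ICC 0.1 and SD of gait-speed change 0.20 m/s, so the facility-level SD is √0.1 × 0.20 = 0.063 m/s. Assumed, because the documents give neither: the share of staff judged ready in each arm, and the correlation r between a latent readiness trait and the facility's mean gain.

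The mean of a standard normal trait among the top share p is φ(z)/p:

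- top 30%: 1.159
- top 40%: 0.966
- top 60%: 0.644

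If 60% pass for Standard, the gap is 1.159 − 0.644 = 0.515 SD when 30% pass for On the Move, and 0.966 − 0.644 = 0.322 SD when 40% pass. Bias = gap × r × 0.063:

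| On the Move pass rate | r = 0.3 | r = 0.5 | r = 1 |
|---|---|---|---|
| 40% | 0.006 | 0.010 | 0.020 |
| 30% | 0.010 | 0.016 | 0.033 |

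At r = 0.3 to 0.5 this is 6 to 16% of the 0.10 m/s target. Swapping the two pass rates reverses the sign.

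**4. Effect on the test.** A simulation assumed 17 facilities per arm, 9 completers per class, ICC 0.1, SD 0.20 m/s and no true effect:

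| Pass rate, On the Move / Standard | r | Bias (m/s) | Type I error |
|---|---|---|---|
| 35% / 35% | 0 to 1 | about 0 | about 5% |
| 25% / 50% | 0.3, 0.6, 1.0 | 0.010, 0.018, 0.030 | 5.5%, 6.3%, 10.0% |
| 30% / 70% | 0.3, 0.6, 1.0 | 0.013, 0.025, 0.042 | 5.6%, 8.1%, 16.1% |

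Bias needs both unequal pass rates and a non-zero correlation.

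**The case against.** The best defence is that Version 2.0 has already demoted Aim 2. Sections 1.2, 9.2 and 9.3.3 call it exploratory and conditional on feasibility, and the confirmatory claim rests on Aim 1. This stands, and it lowers the weight of the point. But the plan ties the label to uncertainty about recruiting and training staff. It never mentions selection after randomisation, and it keeps the formal tests and the effectiveness wording.

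The second defence is that differential selection is conjecture. The four readiness considerations are worded identically for both programs, and three are not about program content. The only relevant experience in the documents, one pilot staff member in Section 2, is of someone who felt confident to lead and progress On the Move after six weeks. This also stands: unequal pass rates are plausible, not shown.

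The third is size. The standard error of the gait-speed contrast is 0.20 × √(2/60) = 0.037 m/s without clustering. With 54 completers per arm and the plan's design effect of 1.90 (54/1.90 = 28.4 effective) it is 0.20 × √(2/28.4) = 0.053 m/s. A bias of 0.006 to 0.016 m/s is then about 0.1 to 0.4 standard errors, and baseline adjustment may absorb part of it. That is fair for moderate correlations.

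Finally, pooling all second-phase participants answers a different question from Aim 2, which asks about staff delivery. That is right, and it is why the pooled analysis belongs among the sensitivity analyses.

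**Conclusion.** The point holds as a limit on interpretation. The staff-led program contrast conditions on an event after randomisation that may differ by program. It is formally tested as effectiveness under a stated intention-to-treat principle, and no as-randomised comparison is specified. That follows from Sections 3, 8.2, 9.1, 9.3.1 and 9.3.3 and needs no assumed figure.

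The size and direction of any bias cannot be known from the documents. It is about zero with equal pass rates. It is about 0.006 to 0.016 m/s for gait speed under assumed pass rates of 60% versus 30 to 40% and correlations of 0.3 to 0.5.

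A reader might infer that On the Move is harder to qualify for, so that the contrast is biased in its favour. The documents give no pass rates and do not support that. A reader might also infer that the programs are no longer randomised. They are: facilities keep their assigned program, and what is lost is the protection of randomisation within the staff-led subset. Aim 1's definition as a randomised comparison of leader-led classes is not what is questioned here.

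**What to change.** 1. **Section 9.3.3, Aim 2.** Keep the staff-led contrast. State that it is conditional on readiness judged after randomisation, is not protected by randomisation, and is not a formal test of effectiveness.
2. **Section 9.3.3, sensitivity analysis.** Compare all participants randomised to the second phase by their facility's randomised program, whoever led the class. Include the classes that 8.2 now excludes or moves to Aim 1. The second baseline and post-intervention assessments are already scheduled for these participants.
3. **Sections 8.2 and 9.3.1.** Reconcile the analysis handling of switched classes with the intention-to-treat statement, and say whether delivery mode is coded as assigned or as delivered.
4. **Reporting.** Tabulate by program the staff identified, judged ready, judged not ready and discontinued. This also serves the plan's own aim of documenting barriers.

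The cost is some wording, one additional model and one table. The drawback is that the as-randomised estimate mixes leader-led and staff-led delivery and shares data with Aim 1. It should be presented as supportive, not as the main Aim 2 estimate.

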## **4 SELECTION AND ENROLLMENT OF PARTICIPANTS**

We will recruit participants from the UPMC Independent Living Facilities (ILFs), other Independent Living Facilities, Senior Housing sites, and Community Centers. Within UPMC there are eight different ILFs with over 700 residents. UPMC is affiliated with 32 different Senior Housing sites that house over 2,000 residents. We anticipate enrolling subjects from 10 ILFs and from approximately 24 of the Senior Housing sites for a total of approximately 34 sites. However, the number of participants per site will vary and we will continue adding sites and enrolling participants until the planned sample size is met for the primary Aim (i.e. n=280).

### **4.1 Inclusion Criteria**

Participants must meet all of the following inclusion criteria to participate in the study.

- 1) 65 years of age or older
- 2) Resident of a UPMC ILF or Senior Housing site
- 3) Ambulate independently for household distances with or with a straight cane,
- 4) Usual gait speed greater than or equal to 0.60 m/s

## 4.2 Exclusion Criteria

Potential participants who meet any of the following exclusion criteria at baseline will be excluded from study participation.

- 1) Non English speaking,
- 2) Impaired cognition, defined as inability to follow 2 step commands or understand the informed consent process,
- 3) Plans to leave the area for an extended period of time over the next 4 months,
- 4) Progressive neuromuscular disorder such as Parkinson's or Multiple Sclerosis,
- 5) Any acute illness or medical condition that is not stable,
- 6) Inappropriate response to the 6 minute walk test (i.e. exercise heart rate  $\geq 120$  bpm, exercise SBP  $\geq 220$  or a drop in SBP  $> 10$  mmHg, or DBP  $\geq 110$  mm Hg).

## 4.3 Study Enrollment Procedures

We will hold information sessions at each of the sites. The study PI ([name]) will visit each site and describe the study to the residents. Subjects who are interested in hearing more will be asked to place their name and phone number on a sign-up sheet. Research staff will then contact the subject to explain the study and conduct the initial phone screen if the subject is interested.

Subject eligibility will be determined from a phone screen and an in-person clinical screen. Researchers will contact potential participants by phone to determine their eligibility. After obtaining verbal consent, a structured screening questionnaire (see attached) will be administered to determine the presence and absence of the inclusion/exclusion criteria. Individuals who meet the criteria will be scheduled for an in-person screening visit that will take place at the ILF or senior housing site.

At the in-person screening visit, the first task will be to obtain informed consent for participation in the study. Once informed consent is obtained, the screening exam will take place. The screening exam will be conducted by trained research personnel (physical therapists, exercise physiologists, physical therapy assistants, or physical therapy students) who have experience working with older adults and conducting such screening measures. ACSM Guidelines regarding exercise participation will be available to all staff during testing. At all screening sessions at least 1 physical therapist will be available as a resource for the other research staff conducting screening procedures.

The purpose of the physical examination is to identify potential exclusion issues that are not identified by self-report. The exam includes a review of systems, current medications, vital signs, lower extremity range of motion and strength testing, and visual screening. A standard demographics questionnaire will be used to determine age, gender, race, marital status and work history in order to adequately describe the research participants. As a screening for exercise participation, all subjects will complete a six minute walk test (additional detail under experimental procedures). Participants will be asked to walk as far as they can in six minutes (without jogging or running) in a hallway. Participants are permitted to stop and rest during this test, if needed, and the number and duration of rest breaks are recorded. Blood pressure, heart rate and level of fatigue (using the rate of perceived exertion (RPE) scale) are recorded before

and after the test. Based on the ACSM guidelines, subjects who have an inappropriate exercise response (i.e. exercise heart rate  $\geq 120$  bpm, exercise SBP  $\geq 220$  or a drop in SBP  $> 10$  mmHg, or DBP  $\geq 110$  mm Hg) will be referred to their primary care physician for clearance before they can be enrolled in the study.(34) Subjects who have an appropriate exercise response and are eligible based on the other screening criteria will then complete the outcome measures of function, disability and walking ability described below. All subjects will sign a “Liability Waiver Release for Participation in an Exercise Program” prior to starting the exercise program.

